## Abstract

**Background:**

Acute ischemic stroke (AIS) is an acute brain injury caused by sudden occlusion of a blood vessel. Endovascular therapy is the most effective way to restore blood flow. However, despite the restoration of blood flow in some patients, their clinical prognosis often remains unsatisfactory. Albumin has shown neuroprotective effects in animal models of AIS. Therefore, this study aims to evaluate the safety, feasibility, and efficacy of local arterial infusions of 20% human serum albumin solution as an adjuvant therapy after endovascular therapy in patients with AIS.

**Methods:**

This study is a prospective, therapeutic exploratory, non-randomized, open-label, phase 1 clinical trial testing the use of 20% human serum albumin solution injected via the artery immediately after successful reperfusion in patients with AIS. The study is divided into two stages. In the first stage, a single-dose-finding will explore the maximum safe dose according to the 3 + 3 dose escalation principle;, with the maximum dose being 0.60 g/kg. After recanalizing the occluded blood vessel, human serum albumin solution will be injected into the internal carotid artery region through a guiding catheter for 30 min. The second stage involves an albumin adjuvant therapy cohort (AT) and an endovascular treatment lonely cohort (ET). The AT cohort will encompass at least 15 additional participants to complete safety trials at the maximum safe dose determined in the first stage. The ET cohort will include well-matched patients receiving endovascular therapy alone, derived from a contemporaneous prospective registry, who will be excluded from having cardiopulmonary disorders and from receiving any neuroprotective therapy. The primary outcome of this study will be symptomatic intracranial hemorrhage. Efficacy outcomes will include the proportion of patients with the progression of cerebral infarction volume, a modified Rankin Scale of 0–2 on day 90 after randomization. An exploratory secondary outcome will be the analysis of thromboinflammatory and neuroprotective molecule profiles.

**Conclusion:**

This pilot trial aims to explore the safety and efficacy of arterial infusion of an albumin solution after occlusive vessel opening in AIS. The results will provide data parameters for subsequent tests on the arterial infusion of albumin solutions.

**Clinical trial registration:**

ClinicalTrials.gov, NCT05953623.

## Background

Having high rates of morbidity, disability, and mortality, stroke is the second leading cause of death worldwide and the main cause of death in China. Ischemic stroke accounts for approximately 70% of all strokes (1, 2) and is a serious threat to human health and well-being. For acute ischemic stroke (AIS), timely and effective restoration of blood flow is one of the main factors influencing good clinical prognosis (3). Endovascular therapy (EVT) can effectively restore occlusive blood flow, significantly reduce the mortality and disability rate of AIS, and is an effective modality to treat AIS (4). However, although >50% of patients who received EVT successfully achieved vascular recanalization, they did not achieve a good clinical prognosis (5, 6). Therefore, adjuvant neuroprotection based on EVT has become a potential treatment for AIS.

The occurrence and development of AIS involve various pathophysiological processes, including excitotoxicity, oxidative stress, inflammatory response, calcium overload, and apoptosis (7, 8). Therapeutic effects can be achieved by intervening in one or more of the pathophysiological processes of AIS. Exploring convenient, safe, and effective neuroprotective therapies is necessary to improve the prognosis of patients with ischemic stroke.

Albumin is a single peptide chain comprising 586 amino acids folded into three domains, with a molecular weight of approximately 67 kDa. It is the most important protein in human plasma, serving various bodily functions such as combining and transporting lipids and lipid-soluble substances, supplementing nutrition, and maintaining plasma colloid osmotic pressure (9). Recently, albumin has been found to exert a neuroprotective effect on the occurrence and development of ischemic stroke. Its neuroprotective mechanisms include antioxidant, anti-inflammation, and anti-edema functions, maintenance of vascular permeability, and regulation of glial cell metabolism (10).

In a mouse model of AIS, a low-dose local arterial infusion of 20% human serum albumin solution was shown to significantly reduce the cerebral infarct volume and alleviate the neurological dysfunction caused by middle cerebral artery occlusion (11). These results suggest that local arterial infusion of 20% human serum albumin solution may benefit the recovery of neurological function after ischemic stroke. However, no clinical trials on local arterial infusion of human serum albumin solution have been conducted to date.

Local intra-arterial administration can help the drug rapidly achieve high local concentrations at the site of action, maximizing its therapeutic effect (12). Based on the neuroprotective effect of albumin and the development of EVT technology, we hypothesize that local arterial infusion of 20% human serum albumin solution will improve nerve function recovery in patients. This study will test the safety, feasibility, and effectiveness of local arterial infusion of 20% human serum albumin solution, based on an intravascular treatment of the responsible occlusive vessels.

## Methods

This study was registered with ClinicalTrials.gov on 20/07/2023 (ID: NCT05953623). The safety of the participants will be monitored continuously by the Ethics Committee of Tianjin Huanhu Hospital.

### Study design

This is a prospective, therapeutic exploratory, non-randomized, open-label, phase 1 clinical trial for testing the use of 20% human serum albumin solution injected via the artery immediately after successful reperfusion in patients with AIS.

### Participants and screening

Patients undergoing EVT at the Department of Neurosurgery of Tianjin Huanhu Hospital between August 2023 and May 2024, who meet the enrollment criteria, will be included in this study. Participants will be continuously enrolled into the study group after confirming recanalization of the occluded blood vessels. Each participant or their designated legal representative will review the written informed consent form, which explains the potential procedural benefits and risks. After the participant or the designated legal representative signs the informed consent form, an independent doctor, not involved in the study will perform an evaluation according to the enrollment criteria. If the participant lacks decision-making ability, the designated legal representative will sign the informed consent. The test procedure is shown in Figure 1.

**Figure 1 fig1:**
[figure not shown]
Flowchart of the first stage of the study.

The inclusion criteria are as follows: (1) age 18–80 years; (2) an anterior circulation large vessel occlusion confirmed using computed tomography (CT), magnetic resonance imaging/magnetic resonance angiography (MRI/MRA), or digital subtraction angiography (DSA); (3) a baseline National Institutes of Health Stroke Scale (NIHSS) score ≥6; (4) an arterial puncture was performed within 24 h of stroke onset (defined as either the time the onset of a neurological abnormality was observed the time when symptoms were first noticed on waking from sleep or the last time the patient was observed to be without stroke symptoms); and (5) the occluded vessel reaches an expanded thrombolysis in cerebral infarction (eTICI) score ≥2b after EVT was confirmed using DSA.

The exclusion criteria are as follows: (1) a history of congestive heart failure or jugular dilatation, third heart sound, resting tachycardia due to heart failure (>100 beats/min), or hepatomegaly and lower limb edema without obvious cause on physical examination at admission; (2) hospitalization for acute myocardial infarction within 3 months; (3) symptoms of acute myocardial infarction or admission electrocardiogram data; (4) second- or third-degree heart block or arrhythmia with hemodynamic instability; (5) acute or chronic renal failure (blood creatinine >2.0 mg/dL); (6) severe anemia (hematocrit <32%); (7) clinically suspected aortic dissection; (8) symptoms or CT evidence of subarachnoid hemorrhage; (9) parenchymal cerebral hemorrhage; (10) pregnancy; (11) allergy to albumin; (12) blood pressure >185/110 mmHg on admission; (13) presence of major lung disease; and (14) presence of other life-threatening diseases.

### Randomization and blindness

The study will be divided into two stages: a first-stage dose-escalation test and a second-stage safety test conducted with an expanded sample size based on the first stage. In the first stage, three participants will be included in each dose group according to the 3 + 3 dose increment principle (13). Seven dose groups will be set in this stage: 0.25, 0.35, 0.40, 0.45, 0.50, 0.55, and 0.60 g/kg. As this study is the first to use a local arterial infusion of 20% human serum albumin solution in humans, the highest dose will be set at 0.60 g/kg. Phase 2 will enroll at least 15 additional participants who will be administered the highest safe dose level determined from phase 1 (14). The Data Security Monitoring Board will conduct a mid-term review at the end of phase one. The protocol is designed as an open-label treatment; thus, we will employ partial blinding; that is, the clinical evaluator will be blinded, but the operator and participant will not be blinded.

### Interventions

All participants will be recanalized after completing EVT with responsible occlusive vessels of ≥2b, as confirmed by DSA. Participants will receive 20% human serum albumin solution (China Resources Boya Biopharmaceutical Group Co., Ltd.) corresponding to their dosage group and individual body weight. Albumin will be injected into the diseased side of the internal carotid artery with an infusion time of 30 min. The patient’s blood pressure, heart rate, respiratory rhythm, and oxygen saturation will be monitored throughout the transfusion process. The operative method for the participants will be determined independently by the neuro-interventional physician, who will choose either mechanical thrombectomy or stent insertion according to the intraoperative conditions. All participants will be treated in accordance with the latest Chinese clinical Guidelines for AIS.

### Outcomes and assessment procedures

The participants’ demographic information will be recorded on the case sheet, including previous medical history, time of onset and progression of stroke symptoms, location of responsible occlusive vessels, and course of intravascular therapy. Head MRI and MRA will be performed to determine the location of the cerebral infarction and the occluded blood vessels. All participants will be required to complete chest CT, hematology, and NIHSS testing before enrollment. CT scans of the chest and head will be performed within 2–24 h after EVT. Head MRI will be performed 3 days after surgery and the infarct volume will be calculated and compared to baseline. NIHSS scores will be measured at 24 h, 48 h, day 7, or at discharge. The NIHSS, modified Rankin Scale (mRS), and Barthel index will be assessed at day 90. The participants will undergo hematological examinations at baseline and within 24 h after surgery, including routine blood tests, blood biochemistry, coagulation studies, and cardiac function-related indicators.

Primary outcomes (safety assessment): the primary safety consideration of the trial is the risk of symptomatic intracranial hemorrhage (sICH). The secondary safety outcomes are: (1) intracranial hemorrhage; (2) all-cause mortality; (3) adverse events; (4) serious adverse events; and (5) heart failure, pulmonary interstitial edema, and severe allergic reactions to albumin infusion.

Secondary outcomes (efficacy assessment): (1) the proportion of patients with an mRS of 0–2 on day 90 after surgery; (2) the development of a cerebral infarct on day 3 after surgery; and (3) changes in NIHSS scores on day 7 after surgery.

Exploratory terminal: (1) coagulation function and blood count related to platelet and lymphocyte counts; (2) biochemical markers of thrombophilic inflammation, including interleukin-1α, interleukin-1β, interleukin-6, interleukin-10, interleukin-18, transforming growth factor-β, histamine, 5-hydroxytryptophan, TNF-α, coagulation factor XII (FXII), ADAMTS13, vWF, GP VI, GP IIbIIIa, tissue factor and soluble CD40 ligand (CD40L); (3) plasma proteomic profiling of subjects; (4) detection of antithrombotic properties of different doses of albumin by peripheral blood cultures of PBMC or platelet cultures from patients or volunteers.

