### Statistical analyses

Statistical analysis will be conducted based on the intention-to-treat principle. Continuous variables will be described using the mean or interquartile range for normal distribution. Categorical variables will be expressed as the frequency and percentage. In this study, multiple independent groups will be compared. The Kruskal–Wallis *H* test and the Mann–Whitney *U* test will be used for severely skewed continuous variables, and the t-test will be used for normally distributed continuous variables. The chi-squared test or Fisher’s exact test will be used to compare the difference in binary outcomes between the groups. All statistical tests will be conducted using a two-sided test. A value of *p* < 0.05 will be considered statistically significant. All statistical analyses will be performed using SPSS statistical software, version 26.0.

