Albumin is widely used in clinics and has been found to have neuroprotective effects in animal models of transient and permanent ischemic stroke (29, 30). Through imaging examination of animal models, the neuroprotective effect of albumin was shown to be related to the normalization of signals on MRI diffusion-weighted imaging and the reduction of necrotic changes in the residual injury area (31). In focal ischemic stroke, albumin can reduce the total infarct volume by two-thirds, reduce cerebral edema by three-quarters, improve microvascular perfusion, transport free fatty acids to the infarct area, and extend the treatment window to 4 h (32–34). An important component of albumin’s protective effect is thought to be exerted through intravascular and anti-inflammatory mechanisms, which include hemodilution; beneficial interactions with the vascular endothelium (8); platelet anti-aggregation (9); antagonism of erythrocyte sedimentation (10) and neutrophil-endothelial binding (11); and binding to the local release of nitric oxide, which reduces the concentration of inflammatory mediators, such as free radicals interleukins.

In preclinical and clinical trials of albumin, intravenous infusion of medium and high doses of 25% human serum albumin solution demonstrates a neuroprotective effect in AIS which increases with increasing doses up to 2.05 g/kg (35). However, including additional participants in phase III showed that intravenous administration of a 25% human serum albumin solution at 2.0 g/kg was not associated with the 90-day clinical outcome but was associated with an increased incidence of cerebral hemorrhage and pulmonary edema (36). In a follow-up study, the negative phase III results were found to be caused by the absence of factors controlling vascular recanalization and the high albumin solution dose. Medium- and high-dose hypertonic human albumin solutions carry the risk of causing serious dose-related adverse reactions. In animal model experiments, local arterial infusion of a low-dose (20%) human serum albumin solution showed a good neuroprotective effect (11).

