With the development of EVT, neuroprotective therapies are also changing. Due to high reperfusion success rates, EVT is currently recommended as the basis for any trial evaluating the neuroprotective effect of stroke caused by large vessel occlusion (37). Most recent clinical trials evaluating adjunctive therapies in combination with EVT have shown greater neuroprotective benefits. In clinical trials of local arterial cooling infusion, the experimental group showed a greater improvement in clinical neurological function than the control group (38). Arterial infusion of nitroglycerin significantly improved the clinical prognosis of patients (39).

A 20% solution of human serum albumin is hyperosmolar and can rapidly increase the blood volume by four to five times the amount of infusion (40). A low-dose local arterial infusion of 20% human serum albumin solution can quickly and safely achieve a high drug concentration in the infarction area, producing a greater neuroprotective effect. Before the clinical trial, a 20% human serum albumin solution was injected into the pharyngeal ascending artery area of normal experimental pigs at 0.50 and 0.60 g/kg, in Supplementary Figure S1. The experimental results did not show any cardiopulmonary function impairment. These experimental results will be published with the results of this clinical trial. Following previous results (41) and under the prerequisite of participant safety, the highest dose in this study is set at 0.60 g/kg.

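### Raw blood counts and soluble plasma markers taken after the infusion are open to dose-dependent dilution by the albumin itself; report dilution-corrected values beside them and record the draw time

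*Protocol article*

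**What the plan says.** All references are to the protocol article.

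- **Endpoints.** Outcomes and assessment procedures lists four exploratory items. The first two are "coagulation function and blood count related to platelet and lymphocyte counts; (2) biochemical markers of thrombophilic inflammation", the second naming 16 markers (interleukins, TNF-α, FXII, ADAMTS13, vWF and others). The third is plasma proteomic profiling. The fourth is a cell-culture assay.
- **Sampling.** The same section plans "hematological examinations at baseline and within 24 h after surgery, including routine blood tests, blood biochemistry, coagulation studies". It gives no narrower time after the infusion and no separate draw time for cytokines or proteomics.
- **Dose and product.** Randomization and blindness: "Seven dose groups will be set in this stage: 0.25, 0.35, 0.40, 0.45, 0.50, 0.55, and 0.60 g/kg". Interventions: "Participants will receive 20% human serum albumin solution".
- **Volume effect.** The Discussion says the solution "is hyperosmolar and can rapidly increase the blood volume by four to five times the amount of infusion". It also says part of albumin's protection is thought to be "exerted through intravascular and anti-inflammatory mechanisms, which include hemodilution", and later in the same list it mentions lower concentrations of inflammatory mediators.
- **Tests.** Statistical analyses: "The Kruskal–Wallis *H* test and the Mann–Whitney *U* test will be used for severely skewed continuous variables", with the t-test for normally distributed variables, two-sided at 0.05. Biomarkers are not mentioned separately.
- **Comparator.** By the Abstract, the ET cohort receives endovascular therapy alone and comes from a registry. No volume-matched infusion is described, and the article does not say whether the markers are measured in ET.

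**The concern.** Blood counts and soluble plasma markers are amounts per unit volume. If the infusion enlarges that volume, they fall even when albumin has no action on the marker. The fall is ordered by dose and has no counterpart in patients who receive no albumin, so dilution has the same pattern as a treatment effect. It also runs in the direction that the Discussion associates with benefit, since lower mediator concentrations are part of the proposed mechanism. A true rise in a marker could equally be hidden.

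The article supplies the expansion factor and names hemodilution, but connects neither to the marker endpoints. The window of up to 24 h allows draws anywhere from near peak expansion to a day later, so the amount of dilution can also differ between patients for reasons unrelated to dose. At stake is whether the exploratory profiles can separate a thromboinflammatory effect from simple volume expansion. The Abstract says the results will supply parameters for later trials, so the distinction has some use beyond this one.

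**Working it through.** **Inputs from the article.** Doses 0.25 to 0.60 g/kg; 20% solution, read as 0.20 g/mL; expansion four to five times the infused volume; at least 15 patients in the second-stage albumin (AT) cohort; 3 patients per dose in the first stage, 6 if a dose group is expanded; two-sided 0.05.

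**Assumptions, not in the article.** Plasma volume V = 40-45 mL/kg; blood volume V = 70 mL/kg; the added volume carries none of the marker; residual expansion of one to two times for a late draw; log-scale SD 0.3-0.8; ET size 15 or 30.

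**The article's own figure.** The four-to-five-times expansion is a cited input and cannot be re-derived here. It is taken as given.

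**Step 1, infused volume** = dose / 0.20.
- 0.25 / 0.20 = 1.25 mL/kg
- 0.60 / 0.20 = 3 mL/kg

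**Step 2, expansion** E = 4 to 5 × infused volume.
- 0.25 g/kg: 5 to 6.25 mL/kg
- 0.60 g/kg: 12 to 15 mL/kg

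**Step 3, passive fall** = E / (V + E).

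| | 0.25 g/kg | 0.60 g/kg |
|---|---|---|
| Plasma marker, smallest (V = 45, 4×) | 5/50 = 10% | 12/57 = 21% |
| Plasma marker, largest (V = 40, 5×) | 6.25/46.25 = 13.5% | 15/55 = 27% |
| Cell count (V = 70, 4×) | 5/75 = 7% | 12/82 = 15% |
| Cell count (V = 70, 5×) | 6.25/76.25 = 8% | 15/85 = 18% |

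**Step 4, late draw at 0.60 g/kg.** With one to two times expansion left, E = 3 to 6 mL/kg. Plasma: 3/48 = 6% to 6/46 = 13%. Cells: 3/73 = 4% to 6/76 = 8%.

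**Step 5, can this reach significance between AT and ET?** This matters only if ET samples exist. At 0.60 g/kg and V = 40, the log shift is ln(52/40) = 0.262 at 4× and ln(55/40) = 0.318 at 5×. It is ln(43/40) = 0.072 at 1× and ln(46/40) = 0.140 at 2×. The table gives the probability of p < 0.05 from dilution alone, with AT = 15, ET = 15 or 30 and a normal approximation.

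| log-SD | 4-5× expansion | 1-2× expansion |
|---|---|---|
| 0.3 | 0.67-0.92 | 0.10-0.31 |
| 0.5 | 0.30-0.52 | 0.06-0.14 |
| 0.8 | 0.14-0.24 | 0.04-0.08 |

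**Step 6, can this give a significant dose-response in the first stage?** I simulated pure dilution across the seven doses with V = 40, 1-5× expansion, log-SD 0.3-0.8 and 3 or 6 patients per dose. The Kruskal-Wallis test gave p < 0.05 in about 1-8% of trials. The top of that range needs six per dose, 5× expansion and log-SD 0.3. With three per dose it stayed at about 3% or below. An exact Mann-Whitney test of 3 against 3 cannot go below p = 0.10.

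**The case against.** **A reader might infer that the investigators will read any fall as an anti-thromboinflammatory effect.** The article does not say so. The Abstract promises only an analysis of molecule profiles, and the Discussion itself lists hemodilution among albumin's mechanisms. What stands is that raw values cannot separate hemodilution from the other mechanisms in that same list.

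**A reader might infer that a dose-response is built in.** A dose-ordered shift in expectation is; a significant one is not, as Step 6 shows.

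**The size at the draw is unknown.** The expansion is described as rapid, the article gives no decay, and the 24 h window is tied to routine, biochemistry and coagulation tests, not expressly to cytokines or proteomics. The 21-27% figure is therefore a peak value. Fluid drawn in from tissue may also carry some marker, which would make the true fall smaller.

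**Marker pre-processing is commonly left to the analysis plan or laboratory manual.** That is correct. The article does not say that raw values will be compared, and the absence of a correction from it is not in itself an error. What remains is the loose draw window and the unconnected dilution figure.

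**Not every endpoint is exposed.** The culture assay is not directly changed by dilution in the patient. GP VI and GP IIbIIIa escape it if measured per platelet, and the proteomic profiling is not stated to be absolute quantification.

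**Correction is imperfect.** Procedural blood loss and other fluids also move hematocrit, and correcting removes a mechanism that the article names. This is a good argument against making the corrected value primary, but not against reporting both.

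**Conclusion.** The concern holds in limited form. On the article's own expansion factor and the assumed volumes, an unaffected soluble plasma marker would fall about 10-14% at the lowest dose and 21-27% at the highest at peak expansion, and cell counts about 7-8% and 15-18%. At 0.60 g/kg with one to two times expansion remaining, the plasma fall is about 6-13%.

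A shift of this size can mimic or mask a biological effect in low-variance markers drawn early. It bears on before-after comparisons in albumin patients, and on AT-versus-ET comparisons if ET samples exist. In noisy cytokines or late draws it would seldom reach significance by itself.

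Severity is low: the endpoints are exploratory, and the primary outcome, symptomatic intracranial hemorrhage, does not depend on them.

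**What to change.** 1. Pre-specify a sensitivity analysis that reports dilution-corrected values alongside raw values for blood counts and soluble plasma markers. The routine blood tests at baseline and within 24 h should supply the hemoglobin (Hb) and hematocrit (Hct) pair.
   - Blood-volume ratio = Hb before / Hb after; multiply post-infusion cell counts by it.
   - Plasma-volume ratio = (Hb before / Hb after) × (1 − Hct after) / (1 − Hct before); multiply post-infusion plasma concentrations by it.
   - Check with blood 70, plasma 40 and expansion 15 mL/kg: red cells are 30 mL/kg, Hct goes from 30/70 to 30/85, and the ratio is (85/70) × (55/85)/(40/70) = 55/40. That restores the marker exactly.
2. Record hours from end of infusion to each draw, for the marker samples as well as the routine tests, and account for it in the analysis.
3. State that a fall will be attributed to an anti-thromboinflammatory effect beyond hemodilution only if it persists after correction. Keep the raw values, because dilution may itself matter for clotting.
4. Apply the same correction to ET samples if they exist. Leave out the culture assay and any per-platelet measure.

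**Cost.** Analysis wording and one time field; no extra blood draw. The correction is approximate where procedural blood loss or other fluids also changed hematocrit, so a corrected value does not isolate the albumin share of the dilution.
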